### Data analysis plan

The data will be analyzed by SPSS 16.0 (SPSS Inc., Chicago, IL, USA). The analysis will be conducted using intention-to-treat principles. The primary outcome, the live birth rate, will be compared between two groups using the Pearson chi-square test; secondary outcome parameters, such as the pregnancy rate, OHSS rate, and other rates, will be analyzed using the Pearson chi-square test. A per-protocol analysis will be performed according to the actual participants completing the entire trial. Continuous data are expressed as mean ± standard deviation, with Student’s test for data with normal distribution and Wilcoxon rank-sum test for nonnormal distribution. Categorical data are represented as frequency and percentage with chi-square analysis or Fisher’s exact test for expected frequencies less than 5. *P* < 0.05 will be considered significant.

The reasons for missing data will be recorded, and according to these reasons, four approaches may be considered: complete-case analysis, single imputation methods, estimating-equation methods, and methods based on a statistical model.

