## Methods/design

### Design and setting

This study is a multicenter, randomized placebo-controlled, double-blind clinical trial to evaluate whether orlistat treatment for 1–3 months before IVF-ET can improve the live birth rate. Patients are recruited from 19 hospitals in China. In this study, overweight is defined as BMI ≥ 25 kg/m^2^ and obesity as BMI ≥ 28 kg/m^2^ according to Chinese criteria.

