### Sample size

Based on the retrospective data from our IVF clinic, the live birth rate of obese or overweight women is about 35%. It is assumed that an improvement of 10% in the live birth rate will be clinically significant. We aim to test a difference of 10% in the live birth rate between treatment groups (45% in the orlistat group) at a significance level of 0.05 with a statistical power of 80%. The minimal sample size calculated is 752, and 836 participants will be enrolled in consideration of a dropout rate of 10%.

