### Randomization and blinding

A total of 836 patients will be enrolled, and a computer-generated random list generated by SPSS 16.0 (SPSS Inc., Chicago, IL, USA) will be used for randomization. The packaging is marked according to the random number list; the packaging and tablets of orlistat (Huadong Pharmaceutical Co., Ltd) and the placebo have the same appearance, which cannot be distinguished. The placebo is manufactured by Huadong Pharmaceutical Co., Ltd, and, in addition to the active ingredients, the rest of the excipient and the appearance and odor are exactly the same as orlistat. The random number list is kept strictly confidential by the Data Coordination Committee (DCC) staff, and the researchers who are in charge of the enrollment have no access to the list. Study personnel are blinded to upcoming treatment group allocation. Participants will receive the medication (orlistat or placebo with a 1:1 ratio). The appearance of orlistat and placebo is identical in packaging, and the participants and all research staff do not know the allocation until the end of the study. The quality of the placebo, such as contents and bacteria contaminations, was controlled rigorously according to the GMP standard.

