### Outcome and outcome assessments

The primary outcome is live birth after first fresh embryo transfer. The secondary outcomes include changes of body weight, moderate and severe ovarian hyperstimulation syndrome (OHSS), dose of gonadotrophin during ovarian stimulation, numbers of oocytes, embryos of high quality, conception, clinical pregnancy, ongoing pregnancy, miscarriage, pregnancy and perinatal complication, birth weight, neonatal complication, and other adverse events.

Conception is defined with the result of serum β-hCG ≥10 mIU/ml measured 2 weeks after embryo transfer.

Clinical pregnancy is defined as detection of a gestational sac in the uterine cavity by a transvaginal ultrasound scan 20 days after conception confirmation.

An ectopic pregnancy is defined as a complication of pregnancy in which the embryo implants at any site other than the endometrial lining of the uterine cavity.

Ongoing pregnancy is defined as detection of a viable fetus with fetal heartbeat at 11–12 weeks of gestation.

Miscarriage is defined as pregnancies that eventuate in a spontaneous abortion before 20 weeks of gestation.

A live birth is defined as the delivery of any number of newborns at ≥ 28 weeks of gestation with heartbeat and breath.

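### Low-cost improvement: prespecify adjustment for age, baseline BMI and hospital in the live birth analysis, and for baseline weight in the weight-change analysis

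*Protocol article*

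**What the plan says.** The Data analysis plan section fixes the primary comparison: "The primary outcome, the live birth rate, will be compared between two groups using the Pearson chi-square test". The other rates are handled the same way. Continuous data are summarised by mean and standard deviation, "with Student’s test for data with normal distribution and Wilcoxon rank-sum test for nonnormal distribution". The section names no covariate and no hospital term.

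Under Outcome and outcome assessments, "The secondary outcomes include changes of body weight". Weight change has no method of its own, so it falls under the general rule for continuous data.

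The baseline information is available:
- Age is an eligibility criterion (20 to 40 years).
- Height and body weight are recorded after consent (Data collection and management).
- Hospital is known: "Patients are recruited from 19 hospitals in China" (Design and setting).

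The Interventions section leaves the stimulation protocol to the physicians, and embryo grading, freezing and luteal support to local practice. Allocation uses "a computer-generated random list generated by SPSS 16.0" (Randomization and blinding), and no stratification factor is mentioned.

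On size, the Sample size section says: "The minimal sample size calculated is 752, and 836 participants will be enrolled in consideration of a dropout rate of 10" percent.

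**The concern.** The trial enrols women over a 20-year age span, with no upper BMI limit, at many hospitals whose practice may differ. If these factors predict live birth, an unadjusted comparison leaves explainable variation in the error term. A chance imbalance in them also passes directly into the estimate. That matters most when the result lies near the significance boundary. An adjusted analysis first proposed after unblinding could be criticised as chosen with the result in view. For weight, the change score subtracts baseline but does not use the correlation between baseline and follow-up fully. What is at stake is modest efficiency and robustness, not validity.

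**Working it through.** **Inputs from the article.** Live birth 35% on placebo and 45% on orlistat, alpha 0.05, power 80%, dropout 10% (Sample size); 1:1 allocation (Randomization and blinding); 19 hospitals (Design and setting). The sidedness of alpha is not stated; two-sided reproduces the stated number.

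**Assumed, because the article gives no figure.** The share R² of live birth variance explained by age, BMI and hospital: 0.02 to 0.10. The baseline/follow-up weight correlation ρ: 0.90 to 0.98. The SD of age: 4 to 5 years.

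**1. The plan's own figure.** With pooled variance and no continuity correction,

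n per arm = [1.960·√(2·0.40·0.60) + 0.8416·√(0.35·0.65 + 0.45·0.55)]² / 0.10² = (1.3579 + 0.5800)² / 0.01 = 375.6, rounded up to 376.

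The total is 752, and 752/0.9 = 835.6, rounded up to 836. Both stated figures are reproduced. The calculation is for the unadjusted test that is planned.

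**2. Gain for live birth.** Adjustment multiplies the variance of the risk difference by (1 − R²). At 376 per arm,

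power = Φ{[0.10 − 1.96·√(0.48/376)·√(1−R²)] / [√(0.475/376)·√(1−R²)]},

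95% half-width = 1.96·√(0.475/376)·√(1−R²).

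| R² (assumed) | Power | Equivalent saving, of 752 women | 95% half-width, points |
|---|---|---|---|
| 0 | 80.0% | 0 | 6.97 |
| 0.02 | 80.8% | 15 | 6.90 |
| 0.05 | 82.0% | 37 | 6.79 |
| 0.10 | 84.0% | 75 | 6.61 |

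If all 836 women contribute, power is 84.0% unadjusted and 84.8% to 87.6% over the same R² range.

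**3. Check by simulation.** Each setting had 3,000 trials of 752 women. The chi-square test was compared with logistic regression on age, BMI and 18 hospital indicators. Assumed log odds ratios per SD were −0.2, −0.3, −0.45 for age and −0.1, −0.15, −0.2 for BMI, with a hospital SD of 0.2, 0.3, 0.4 on the logit scale.

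| R² (approx.) | Power, unadjusted | Power, adjusted | Type I error, unadjusted | Type I error, adjusted |
|---|---|---|---|---|
| 0.02 | 80.6% | 80.9% | 5.2% | 5.4% |
| 0.04 | 80.0% | 82.1% | 5.2% | 5.0% |
| 0.08 | 79.6% | 82.6% | 4.3% | 4.7% |

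The gain is about 0 to 3 points. Both tests are at the nominal level within simulation error (standard error about 0.4 points).

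**4. Chance imbalance.** A share R² of the variance of the unadjusted difference comes from imbalance in these factors. The 95% range of the resulting shift is therefore ±6.97·√R²: ±1.0, ±1.6 and ±2.2 points at R² of 0.02, 0.05 and 0.10. The target difference is 10 points. An observed difference reaches significance at about 1.96·√(0.48/376) = 7.0 points. For age alone, the 95% range of the difference in means is ±1.96·SD·√(2/376), or ±0.6 to ±0.7 years.

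**5. Weight change.** With equal SD σ at both times, the change score has variance 2σ²(1−ρ) and ANCOVA has σ²(1−ρ²), a ratio of (1+ρ)/2. This is 0.95 at ρ = 0.90 and 0.99 at ρ = 0.98, a reduction of 5% to 1%. Even at ρ = 0.70 it is 0.85, a reduction of 15%.

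**The case against.** The strongest reply is that nothing here is wrong. The chi-square test keeps its type I error, it is the test behind the sample size, and its error rate already allows for chance imbalance over repeated randomisations. All of that stands.

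The size of the benefit also rests on assumptions. The Background compares women above and below a BMI of 25, which says nothing about a gradient among the women enrolled. The Interventions section shows that practice may differ between hospitals, not that live birth does. With weak predictors the gain is close to zero. For weight, baseline is already subtracted, so little remains to be gained.

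Adjustment is also not free. Nineteen hospitals average about 40 evaluable women each (752/19), and some may be small. A logistic odds ratio is not the planned comparison of rates unless it is standardised. More than 350 women had been enrolled when the article was written, so replacing the primary test is a real change to the plan.

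These points limit the claim but do not remove it. The stated method is less efficient than one that uses data already in hand, and the practical difficulties have standard solutions.

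A reader might also infer that randomisation was unstratified, or that no effect size or interval will be reported. The documents do not support either inference. A condensed article is silent on both, and such details are commonly left to the full protocol or analysis plan.

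**Conclusion.** This is an inexpensive improvement, not an error. The plan fixes an unadjusted test for live birth and, through its general rule, an unadjusted test for weight change, although useful baseline values are known before treatment.

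The expected gain is modest: about 1 to 4 power points by formula for R² of 0.02 to 0.10, and a 1% to 5% reduction in variance for weight change. The protection is against shifts of roughly 1 to 2 points in the live birth difference. The direction is secure. The size depends on R² and ρ, which the documents do not give, so confidence is moderate.

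It would go too far to say that the chi-square result would be invalid, or that adjustment would rescue an underpowered trial. The test holds its level and the stated sample size is correct for it.

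**What to change.** Before unblinding, prespecify the following:

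- **Live birth:** a logistic model with treatment, age and baseline BMI (both continuous) and hospital, with small hospitals pooled by a stated rule or hospital as a random effect. Report the standardised risk difference with its 95% confidence interval. Keep the Pearson chi-square test as the supporting analysis.
- **Weight:** ANCOVA of follow-up weight (or weight change) on treatment and baseline weight.
- **Randomisation:** if the list was stratified, include the stratification factors in the model. If an analysis plan that is not shown already contains an adjusted analysis, align the two documents.

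The sample size stays at 752 evaluable and 836 enrolled, and no new data are needed. The cost is slightly more analysis work, a rule for sparse hospitals, and a dated, documented change to the primary analysis. The article says that allocation stays concealed from participants and research staff until the end of the study, so the change can be made without knowledge of results.

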**Fig. 1 Fig1:**
[figure not shown]
SPIRIT diagram for schedule of enrollment, interventions, and assessments. Safety assessment includes fasting blood glucose, insulin, TG, TC, HDL, LDL, Lp (a), liver function, renal function, CBC, coagulation test, HBV, HCV, HIV, syphilis, and routine urine. t1, 1–3 months after allocation; t2, day of ET; t3, 2 weeks after ET; t4, 5 weeks after ET; t5, 10 weeks after ET; t6, 28 weeks of gestation; t7, 37 weeks of gestation; t8, delivery; t9, 6 weeks after delivery

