### Interventions

Participants are randomized to receive either orlistat 120 mg p.o. three times daily (intervention) or placebo 120 mg p.o. three times daily after signing consent at the screening visit. Both groups of participants will take orlistat or placebo for 1–3 months before ovarian stimulation and to the day of fresh embryo transfer.

The protocol of ovarian stimulation is decided by the physicians according to the patients’ characteristics. Oocyte retrieval is performed 34–36 h after human chorionic gonadotrophin (hCG) injection by experienced physicians, and oocytes are inseminated by IVF or ICSI according to the quality of sperm. On day 3 or 5 of the embryo culture, the quality of embryos is assessed by experienced embryologists, and the morphological criteria are selected by the local laboratory. No more than three embryos on day 3 or 5 will be transferred, and the rest of the embryos will be frozen according to local experience. The protocol of luteal phase support and the day of starting will be determined by the local center. The serum hCG test is performed after 2 weeks of transfer, and if the test is positive, follow-up will be continued to the end of pregnancy or delivery.

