### Data collection and management

To ensure the accuracy of outcome assessments and data collection, all of the physicians, nurses, and research assistants will attend a training workshop before the start of the trial. All attenders will be provided with a protocol and standard operation procedures, and will discuss the topics they may feel confused about until everyone is totally clear about the procedures. The DCC is responsible for the monitoring tasks of the trial. Personnel of Shandong University will regularly check the data from different sites, determine the issues that affect the quality and speed of research, and take corresponding measures.

After screening and signing of informed consent, the current medication status, previous medical history, height, body weight, waistline, hipline, blood pressure, transvaginal ultrasound scan, and basal sex hormones will be recorded.

OHSS, dose of gonadotrophin, and information on oocytes and embryos will be assessed from the start of ovarian stimulation to the day of the pregnancy test.

Serum β-hCG will be measured 2 weeks after embryo transfer. If the serum β-hCG test is positive, a transvaginal ultrasound scan will be performed 20 days later to detect the gestational sac.

During pregnancy beyond 12 weeks, participants are contacted by telephone call at 28 and 32 weeks to inquire about pregnancy complications, AEs, and combination therapy.

At delivery, obstetrical and perinatal complications and neonatal information are obtained with reference to obstetric medical records and neonatal medical records.

At 6 weeks after delivery, postpartum complications and neonatal complications are followed up by telephone call.

Data are collected and recorded on a standard case report form, and when the visit is completed in every site, all of the recorded data will be entered into the web-based data system by the double-entry method.

Any participant may quit the trial at any time for any reason. If any patients want to quit, clinicians will ask whether they agree to finish the follow-up according to the trial schedule. All patients who quit and are lost to follow-up will be recorded.

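### The per-protocol set is defined by finishing the trial rather than by taking study drug, and read literally it conditions on pregnancy

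*Protocol article*

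**What the plan says.** The Data analysis plan sets the main principle, "The analysis will be conducted using intention-to-treat principles", and then adds a second analysis: "A per-protocol analysis will be performed according to the actual participants completing the entire trial". That sentence is the whole definition of the per-protocol set in the article.

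Four other places bear on what it means:

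- Outcome and outcome assessments: "The primary outcome is live birth after first fresh embryo transfer".
- Interventions, on exposure: "Both groups of participants will take orlistat or placebo for 1–3 months before ovarian stimulation and to the day of fresh embryo transfer".
- Interventions, on follow-up after the 2-week hCG test: "if the test is positive, follow-up will be continued to the end of pregnancy or delivery". The legend of Fig. 1 ends the schedule with "t8, delivery; t9, 6 weeks after delivery".
- Data collection and management, on withdrawal: "If any patients want to quit, clinicians will ask whether they agree to finish the follow-up according to the trial schedule".

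**The concern.** A per-protocol analysis is meant to describe women who were treated as planned. Here exposure ends at fresh transfer, but membership is decided by what happens afterwards, up to 6 weeks after delivery. That interval contains the primary outcome. The rule also says nothing about how much drug was taken.

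Completion and adherence can part company in both directions. A woman who stops the drug but agrees to be followed can count as a completer. A woman who took every dose and is lost in late pregnancy cannot.

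The result could therefore differ from the intention-to-treat result for reasons unrelated to treatment. Because completion is not defined for women whose course ends early, someone must choose a reading later, and the readings give very different answers.

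**Working it through.** **Inputs from the article.** Live-birth rate 35% on control and 45% on orlistat, significance level 0.05, power 80%, minimum 752, enrolment 836 with 10% dropout (Sample size); 1:1 allocation (Randomization and blinding). The article gives no figure for the per-protocol set.

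**Step 1. The plan's own figure.** Two-sided test of two proportions without continuity correction, mean rate 0.40:

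n per arm = [1.96·√(2·0.40·0.60) + 0.8416·√(0.35·0.65 + 0.45·0.55)]² / 0.10² = (1.358 + 0.580)² / 0.01 ≈ 375.6, so 376 per arm and 752 in total. Then 752 / 0.90 = 835.6, so 836, or 418 per arm. Both stated figures reproduce. The steps below use 35%, 45% and 418 per arm.

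**Step 2. Finishing means reaching delivery or the contact after it.** A woman with a negative test, or who miscarries, never gets there. Let L be the share of deliveries at 28 weeks or later that are live, equal in both arms (assumption: 0.95 to 0.99).

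- Set size per arm = 418 × rate / L.
- Placebo: 418 × 0.35 / 0.95 = 154, down to 418 × 0.35 / 0.99 = 148.
- Orlistat: 418 × 0.45 / 0.95 = 198, down to 418 × 0.45 / 0.99 = 190.
- Live-birth rate within the set = L in both arms, 95–99%. Difference: 0 instead of 10 points.

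**Step 3. Finishing means a positive test followed to the end of pregnancy.** Assume 15–30% of conceptions are lost, equally in both arms. The live-birth rate within the set is 1 − loss, so 70–85% in both arms, and the difference is again 0. Any effect acting through conception has been conditioned away.

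**Step 4. Finishing means not quitting and not being lost.** Women with a negative test stay in. Let d be the proportion not completing, and assume that none of them has a live birth. Rate within the set = rate / (1 − d).

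| Non-completion, placebo / orlistat | True 35% vs 45% | Difference | No effect, 35% in both | Difference |
|---|---|---|---|---|
| 10% / 10% | 38.9% vs 50.0% | 11.1 points | 38.9% vs 38.9% | 0 |
| 5% / 15% | 36.8% vs 52.9% | 16.1 points | 36.8% vs 41.2% | +4.3 points |
| 15% / 5% | 41.2% vs 47.4% | 6.2 points | 41.2% vs 36.8% | −4.3 points |

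**Step 5. False rejection in the second row with no effect.** Set sizes are 418 × 0.95 = 397.1 and 418 × 0.85 = 355.3. SE = √(0.3684·0.6316/397.1 + 0.4118·0.5882/355.3) = 0.0356. z = 0.0433 / 0.0356 = 1.22. The probability of exceeding ±1.96 is then about 0.23, against a nominal 0.05. With equal 10% losses it stays at 0.05.

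The 5%, 10% and 15% splits, and the rule that no non-completer has a live birth, are illustrations. If non-completers had the same live-birth rate as completers in their own arm, Step 4 would show no bias.

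**The case against.** **The literal reading is not the natural one.** Follow-up continues only after a positive test, so a woman with a negative test has arguably finished her own schedule. The withdrawal paragraph contrasts finishing follow-up with quitting or being lost. Nobody would intend a set with almost 100% live births. This stands. A reader might infer that the rule certainly selects women on the pregnancy outcome, but the article does not support that as a fact. It follows only under the readings in Steps 2 and 3.

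**Finishing might include the drug phase.** Study drug is part of the trial course, so a woman who stopped early may not count as having finished. The wording allows this but does not say it, and it sets no threshold. Even then, an adherent woman lost late would be excluded.

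**The per-protocol analysis is secondary.** This stands. The primary comparison and the sample size do not depend on it. The article also does not say that the result would be presented as efficacy under adherence.

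**Dilution from keeping women who stopped the drug.** If 15% of the orlistat arm stopped and had the control rate (assumption), a 10-point effect would shrink to 0.85 × 10 = 8.5 points. The intention-to-treat analysis carries the same dilution, so this shows no harm specific to the per-protocol set, and the point does not rest on it.

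**An article condenses.** Finer criteria may exist in a full protocol or SAP that is not shown. That would excuse silence. But the article states a rule, and the rule as stated does not serve its purpose.

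**Conclusion.** The point holds as a fault in a stated secondary analysis. The per-protocol set rests on an undefined completion criterion, with no explicit requirement on drug intake.

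On the more natural reading it is a post-randomisation completers set. Unequal non-completion can bias it in either direction: 6.2 to 16.1 points around a true 10, or a false gap of about 4.3 points with about 23% rejection under no effect. These sizes depend on the assumed 5% and 15% losses and on all non-completers being without a live birth, so they show what could happen and are not forecasts. On the literal reading the live-birth comparison loses its meaning, given equal live-delivery shares in the two arms.

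The intention-to-treat primary analysis is untouched. The change should be made, but the trial's main conclusion does not depend on it.

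**What to change.** Replace the sentence with a definition that uses only facts fixed before the hCG test:

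- eligible at randomisation;
- assigned study drug taken over the treatment period in the Interventions section, to the day of fresh transfer or to the point where the cycle ended without one, above an adherence threshold that the sponsor sets in advance;
- no major protocol deviation, from a list written in advance. The article excludes users of other weight-reducing drugs only at screening, so on-trial use should not be assumed to be a deviation unless the full protocol says so.

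Keep women in the set whatever their pregnancy result. Count a negative test, a miscarriage or no transfer as no live birth. Handle loss to follow-up by the missing-data plan and not by exclusion. Fix membership before unblinding and label the analysis supportive.

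The cost is one paragraph and a blinded classification of records. The article says that enrolment is ongoing and that allocation stays concealed until the study ends, so on what it reports the change can be made without knowledge of results. One condition is open: the article does not describe how drug intake is recorded. The sponsor must confirm that it is. If it is not, an adherence-based set cannot be built from existing data, and the analysis should be called a completers analysis, with completion defined for each course a woman can take.

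### The named tests for birth weight and neonatal complications take no account of siblings, and the plan does not say whether the unit is the infant or the delivery

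*Protocol article*

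**What the plan says.** Under Outcome and outcome assessments, the secondary outcomes end with "miscarriage, pregnancy and perinatal complication, birth weight, neonatal complication, and other adverse events". Most of the earlier items in that list yield one value per woman. Birth weight and neonatal complication arise once per newborn, and under Data collection and management the neonatal information is drawn from obstetric and neonatal records.

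Multiple births are foreseen. Interventions states: "No more than three embryos on day 3 or 5 will be transferred". The primary outcome is worded to cope with them: "A live birth is defined as the delivery of any number of newborns at ≥ 28 weeks of gestation with heartbeat and breath". It is therefore one event per woman.

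The Data analysis plan chooses tests by type of variable. Continuous data get Student's "test for data with normal distribution and Wilcoxon rank-sum test for nonnormal distribution". For rates, "secondary outcome parameters, such as the pregnancy rate, OHSS rate, and other rates, will be analyzed using the Pearson chi-square test". More generally, "Categorical data are represented as frequency and percentage with chi-square analysis or Fisher’s exact test for expected frequencies less than 5". No exception is made for infant-level outcomes, and nothing is said about correlation within a mother. Estimating-equation and model-based methods do appear in that section, but only as options for handling missing data.

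**The concern.** Student's t, the rank-sum test, Pearson chi-square and Fisher's exact test all treat each value as independent of the others. Siblings from one pregnancy share a mother, a gestation and the fact of being a multiple, so their outcomes are correlated. If two twins are entered as two independent observations, the test credits the trial with more information than it has. Confidence intervals come out too narrow and p-values too small.

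A second, separate issue concerns the estimate itself. If the arms differ in the share of multiple deliveries, mean birth weight over all infants differs for that reason alone, if multiples are lighter. A correct standard error does not show how much of an observed difference comes from plurality.

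At stake is how the neonatal comparisons are read for a treatment that continues to the day of fresh embryo transfer.

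**Working it through.** **The plan's own figure.** Inputs from Sample size: 35% versus 45% live birth, significance level 0.05 (two-sided assumed, since sidedness is not stated), power 80%. With pooled variance and no continuity correction:

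n per arm = [1.960·√(2·0.40·0.60) + 0.842·√(0.35·0.65 + 0.45·0.55)]² / 0.10² = 375.6, rounded up to 376. The total is 752, and 752/0.90 = 835.6, rounded up to 836. Both stated figures reproduce. The calculation counts women, so twins do not enter it.

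**Expected deliveries.** Under the stated rates, 376·0.35 + 376·0.45 = 131.6 + 169.2 = 300.8, or about 150 per arm on average.

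**Effect of sibling correlation.** Let t be the share of deliveries that are twins and ρ the within-pair correlation. Neither is in the protocol, so both are assumed: t = 10–40%, ρ = 0.3–0.9. Triplets are ignored, and twins and singletons are first given the same mean.

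- Infants = 300.8·(1 + t), about 331 to 421.
- Share of infants who are twins = 2t/(1 + t), 18% to 57%.
- Design effect DE = 1 + ρ·2t/(1 + t).
- True two-sided error of a nominal 5% test = 2·[1 − Φ(1.96/√DE)].
- Understatement of the standard error = 1 − 1/√DE.

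| t | ρ | DE | True error | SE too small by |
|---|---|---|---|---|
| 10% | 0.3 | 1.055 | 5.6% | 2.6% |
| 20% | 0.5 | 1.167 | 7.0% | 7.4% |
| 30% | 0.5 | 1.231 | 7.7% | 9.9% |
| 40% | 0.9 | 1.514 | 11.1% | 18.7% |

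The same formula serves a complication rate, with ρ then the within-pair correlation of the yes/no outcome.

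**Simulation check.** The t-test was applied to infants with no treatment effect: 150 deliveries per arm, 10,000 runs per setting, t = 10–40%, ρ = 0.5–0.7, SD 500 g within plurality (assumed). It rejected in 6.0–10.0% of runs when twins and singletons had equal means. When twins were 800 g lighter (assumed), it rejected in 8.4–10.2%.

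**Plurality and the mean.** The shift in mean birth weight over infants equals the weight gap times the difference between arms in 2t/(1 + t). Take the assumed 800 g gap and a five-point difference in twin deliveries:

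- 10% versus 15%: (0.261 − 0.182)·800 ≈ 63 g.
- 25% versus 30%: (0.462 − 0.400)·800 ≈ 49 g.
- 35% versus 40%: (0.571 − 0.519)·800 ≈ 42 g.

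With equal twin shares the shift is zero. With one mean value per delivery, a five-point difference still shifts the mean by 0.05·800 = 40 g, so changing the unit does not remove this component. These figures only illustrate the mechanism; nothing in the protocol says the arms will differ.

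**The case against.** The strongest reply is that the protocol never says infants will be pooled as independent observations. Its test sentences are generic. One birth weight per delivery, any affected infant per woman, or a singleton-only comparison would all fit them and respect independence. A condensed article may also leave the unit of analysis to a fuller document. Most of the secondary list is one value per woman, where twin clustering does not arise.

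The first part of this stands: a reader might infer that the invalid analysis is planned, and the text supports only that it is permitted. The appeal to condensation carries less weight, because the article names the tests, applies them without exception, and includes outcomes that are naturally recorded per infant.

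A reader might also infer that many infants will be twins. The limit of three embryos is a ceiling, not a typical number, and no multiple-birth rate is given. At the low end of the assumed range, the error is 5.6%, close to nominal.

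It would likewise go too far to call a pooled birth-weight difference uninterpretable. It remains a fair description of the total difference among the births, plurality included. Nor do these two outcomes carry the whole safety case: the Safety assessment section collects adverse events separately, including neonatal death up to 6 weeks and congenital anomaly.

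**Conclusion.** The point holds in conditional form. The plan names only tests for independent observations, foresees multiple births, lists infant-level outcomes and leaves their unit unstated. If infants are the unit, the nominal 5% error becomes about 5.6–11.1% over the assumed ranges (7.7% at 30% twin deliveries and a correlation of 0.5), and standard errors are about 3–19% too small. The direction follows from any positive sibling correlation. The size rests wholly on assumed twin rates and correlations.

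The effect is confined to secondary neonatal outcomes. It would be wrong to infer that the primary comparison is compromised: live birth is one event per woman, and the 752/836 sample size stands.

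**What to change.** State the unit of analysis for birth weight and neonatal complications, then choose one of two routes in advance:

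- **Per infant:** GEE, a mixed model or cluster-robust standard errors, clustered on mother.
- **Per delivery:** one value per delivery, for example the mean birth weight of the siblings; for complications, any affected infant per woman. The tests already named can then be kept.

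The two routes weight multiples differently, so the choice should not be made after seeing the data.

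Neither route separates out plurality. Report the multiple-birth rate per randomised woman in each arm, and show birth weight and complications for singletons and multiples separately. Label those tables descriptive, because plurality arises after randomisation and the subgroups are not protected by it. Within the multiples table, siblings still need to be treated as clusters.

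The cost is a few sentences of analysis wording and a few tables, with no new data and no change in sample size. Enrolment was still ongoing when the article was submitted, so the wording could be settled before unblinding.
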